## Abstract

**Background:**

The PHARE-M care quality improvement program, modeled on the US Cystic Fibrosis Quality Improvement Program, was introduced at 14 cystic fibrosis centers (CFCs) in the French Cystic Fibrosis Network between 2011 and 2013. The pilot phase assessments attested the progressive adherence of the teams and improvements in care management. The PHARE-M Performance research project aims at assessing in 2015 the impact of the PHARE-M program on patient health indicators at trained versus untrained centers. It also sought to identify contextual factors that could account for variability in the performance of the PHARE-M among the trained centers.

**Methods:**

A mixed methodology combining:a quantitative experimental study: a comparison, using a mixed model for repeated data (from 2011 to 2015), of the average changes over time in forced expiratory volume in 1 s (FEV1) and body mass index (BMI) between two groups of patients included in a closed cohort (non-transplant patients, continuous follow-up at one participating CFC, and a CF-causing mutation), one having benefitted from the PHARE-M program and the other not having done so, anda realistic study: a characterization of the impact on care management and an identification of mechanisms through which the PHARE-M intervention improved the team’s effectiveness in different CFC contexts; this required modeling the intervention, context, and impact on care management with respect to the criteria of the chronic care model (CCM); this was done using a self-administered questionnaire given to professionals and patients/parents supplemented with focus groups.

**Conclusion:**

Although the study population was controlled, it may be difficult to establish a causal relationship between the differences in the changes over time in patient health indicators in the two groups of patients and the PHARE-M intervention as it is often the case in complex interventions rolled out in adaptive environments. The analysis of factors associated with variations in the impact of the PHARE-M at the different trained CFCs required the adoption of instruments validated in other contexts; these could be useful for assessing the performance of other interventions in healthcare practices at CFCs in France.

## Background

Cystic fibrosis is the most common rare disease affecting the Caucasian population; it afflicts around 6500 individuals in France, 29,000 in the United States, and 11,000 in the United Kingdom. It is an autosomal recessive genetic disease caused by mutations in the cystic fibrosis transmembrane conductance regulator (*CFTR*) gene. Among all identified *CFTR* gene mutations, a list of mutations responsible for cystic fibrosis symptoms has been established and is regularly reviewed by the CFTR2 expert group [1]. Cystic fibrosis mainly affects the respiratory and digestive systems. The thick mucus in the bronchi brings about chronic inflammation and repeated infections, leading to chronic respiratory failure, the major cause of death. The majority of patients have pancreatic insufficiency and show poor nutrient absorption, resulting in an at-risk nutritional status associated with a poorer respiratory state [2]. Since the 1960s, the US Cystic Fibrosis Foundation (CFF) has identified multidisciplinary patient management at specialized centers as an essential factor in care improvement; this has led it to establish criteria for the accreditation of cystic fibrosis centers [3]. In the late 1990s, an increase in the number of adults suffering from cystic fibrosis led the CFF to clarify certain criteria for adult centers by stipulating care management by specialized physicians and a specialized team and a formalized process of transition from a pediatric center to an adult program. The accreditation process not only validates centers but also *"fosters continuous improvement efforts within care centers,"* as *"the expectation that each care center have a QI program in place was added to the accreditation and oversight process in 2004."* In the 2000s, following the publication by the US Institute of Medicine, of the report on the Quality Chasm [4], the CFF launched a benchmarking study across the US CFCs, which showed a difference of several years in the median survival age between the ten centers having the best patient outcomes and the other centers (unpublished study). This led the CFF to develop and implement a Quality Improvement Program (QIP) in the form of Learning and Leadership collaboratives [5–7] with the academic support of The Dartmouth Institute Microsystem Academy (TDIMA). A supplement in BMJ Quality and Safety has been published in May 2014 to present the success of this QI initiative [8].

In 2002, following the generalization of newborn screening in France, the French Ministry of Health designated 49 cystic fibrosis centers (CFCs) [9] and in 2006, the French National Authority for Health (HAS) published the National Diagnosis and Treatment Protocol (PNDS) in Cystic Fibrosis to establish a framework for multidisciplinary care at CFCs. The French public health insurance guarantees that every CF patient is reimbursed 100% for care and authorized drugs related to cystic fibrosis. In 2006, within the framework of the 1st National Plan for Rare Diseases, two centers of expertise for cystic fibrosis were labelled (CF-CERDs), in order to implement six priorities across the CF Network: care expertise, information systems and epidemiology, quality of care, clinical research, network organization and coordination. The Nantes/Roscoff CF-CERD, consisting of the CFCs at the two hospitals in Nantes and Roscoff as well as the transplant center in Nantes and the rehabilitation center in Roscoff, developed its action plan contributing to 5 out of the 6 priorities, covering themes such as therapeutic patient education (care expertise), quality improvement in care processes, information and communication systems, and clinical research on transplantation and in human and social science. The agreement signed by the heads of all CFCs in 2007 included a commitment to *“participate in a quality assessment and improvement program to be offered by the CF-CERDs in collaboration with the French Cystic Fibrosis Society (SFM) and the patient organizations in the next five years”*.

In 2011, the French national team at the Nantes/Roscoff CF-CERD transposed the PHARE-M quality improvement program from the US CFF QIP model (*PHARE-M: Programme Hospitalier d’Amélioration des Résultats et de l’Expertise en Mucoviscidose - Hospital Program to Improve Outcomes and Expertise in Cystic Fibrosis)*. It was launched in September 2011 with a pilot phase (2011–2012) involving seven volunteer CFCs, which underwent two external assessments, leading to certain adjustments to the initial program. This adjusted version was deployed during a regional expansion phase (2012–2013), including seven more CFCs before its national deployment [10]. The main adjustments consisted in more practical exercises during face-to-face meetings (less theoretical presentations), more on-site coaching to help the quality teams analyze their processes of care, and the designation of a PHARE-M referent in each local team to keep focused on the QI work. These 2 years are called the “experimental phase”, which involved 14 CFCs.

The two evaluations at the end of the one-year pilot phase showed the progressive adherence of the teams and improvements in care management, but a limited impact on patient health outcomes. They also highlighted that the adherence to the program mainly depended on the motivation of the multidisciplinary team (MDT), especially its lead physician. The lack of resources at some CFCs was raised to account for variations in the teams’ engagement as the level of available staff seemed to influence the extent to which the team was effectively enlisted. The participation of a patient or parent in each local quality team varied depending on the cultural context of the centers, some being used to share information with patients/parents, having a patient group in the CF center for years, others being involved in patient therapeutic education while others were acting in a more partenalistic model of care. The support received from the hospital quality department in two hospitals was emphasized as a factor that facilitated the adoption of quality tools by the teams. The recommendation of the assessor was to evaluate the impact of the program on patient outcomes by 2015.

Given the innovative nature of the QIP PHARE-M in France, the cultural differences and various organizational contexts at the CFCs, an assessment of the impact of PHARE-M at the CFCs engaged in the experimental phase was expected after 3 years to continue the enrollment in the program. Will it show favorable changes in the patient outcomes in the group of CFCs engaged in the PHARE-M compared to the other CFCs? What impact on care management can be observed in 2015? Was the period sufficient to show improvements in the two areas? In which contexts is the impact of PHARE-M observed to be the strongest? The PHARE-M Performance research project, submitted at a call for projects of the French Ministry of Health and selected for funding in December 2012, aims at providing answers to these questions.

## Methods

### A mixed methodology

The rationale of the PHARE-M Performance project is to show evidence of the performance of the PHARE-M program on patient outcomes and care management.

The study is based on a mixed methodology inspired on the one hand by epidemiology, using data from the French Cystic Fibrosis Registry, and on the other hand by the British guidelines on “Process evaluation of complex interventions” [11]:

1) *a quantitative study* to compare the changes over the 4 years in the patient health indicators of a closed cohort, using data from the French Cystic Fibrosis Patient Registry, between CFCs having benefitted from the intervention during the experimental phase and CFCs not having benefitted from the intervention up to 2015; and.

2) *a qualitative study* to analyze the contextual elements and mechanisms brought into play by the PHARE-M intervention that could account for a difference in impact among trained CFCs either on patient health indicators or on care management assessed according to the criteria of the chronic care model [12].

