**Fig. 3 Fig3:**
[figure not shown]
Modeling of the intervention, context, and mechanisms

The PHARE-M intervention consisted of establishing, training and coaching a quality team (QT) at each CFC comprising a number of professionals from the multidisciplinary CF team and 1 parent or patient from the CFC’s caseload. The members of the QT have been trained in quality methods and tools and coached in changing care processes. The PHARE-M intervention should have directly impacted the ability of the local QT to master QI methods and tools, lead changes in the care processes, and should have generated good appreciation of the utility of the QT efforts. This direct impact of PHARE-M is identified under the heading “QT effectiveness”. QT effectiveness may not only be the result of the PHARE-M intervention but may have been modulated by internal mechanisms, such as the composition of the QT (number of members and disciplines enlisted), its functioning (rigor in the QI work, decision-making, clarity of the roles…) and the parent or patient engagement. Those mechanisms are represented as impacting QT effectiveness (Table 3). Beyond the ability to master the QI methods and tools, the PHARE-M intervention was expected to have an impact on the quality of CF care delivered at the CFC. The Chronic Care Model [12] was deemed appropriate to account for quality of CF care across the 6 dimensions: existing improvement goals, multidisciplinary care, self-management support, decision support (use of evidence-based guidelines), use of information system and electronic patient record, and organization of resources in the patient’s community of life. Finally, an indirect impact of the PHARE-M intervention is expected on the trend in patient outcomes’ evolution as measured in the quantitative part of this study. Moreover, some elements in the CFC contexts, which are external to the PHARE-M intervention and preexisted to its introduction, may have had a major impact both on the adherence of the team to the QI work and on its outputs. The contextual elements that have been brought in this study include the composition of the MDT, the leadership, the patient-centeredness of care, the innovative culture of the team, and the support from the hospital quality department.

The qualitative study will test these hypotheses using a questionnaire to be self-administered, in 2015, to all members of the MDT at the 14 CFCs and to the patients/parents participating in the quality teams.

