### On-site investigations

The investigations conducted by the clinical research assistant at the 14 PHARE-M centers take place over the course of 2.5 consecutive days per CFC. The questionnaire is self-administered successively under the supervision of the clinical research associate according to a schedule established with the team at the site, with no possibility of communication or consultation among respondents. The questionnaires and responses are managed in SurveyMonkey Software and subsequently exploited using SAS and Excel Software. The focus group is conducted at the end of the visit. Each focus group is recorded using audio equipment and transcribed in writing.

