### Analyses of responses and validation of the questionnaire

Responses to the items of the questionnaire are processed anonymously. Each item receives a score on a Likert scale from one to four based on the degree to which the respondent agrees or disagrees with the proposition: “Completely disagree; Disagree; Agree; Completely agree”. “No” and “Unknown” responses are assigned a score of 0. The score is reset to 100 points and can thus be totaled by theme of the questionnaire and category of respondents. An initial descriptive analysis of the responses by CFC is returned to each quality team in the month following the on-site investigation, via a web conference, in order to validate the interpretation of the scores for the different themes and identify avenues for or obstacles to continuous care quality improvement at the CFC.

A Cronbach’s alpha test will be performed on all responses collected at the centers. Since the anticipated number of respondents is around 130 people in total for the 14 teams, this test will not allow the questionnaire to be modified for use in a larger population of respondents. It mainly aims to validate the French translations of the parts of the questionnaire coming from previous studies in English and discuss the use of the parts created within this research study.

A second level of descriptive analysis will be performed by aggregating the responses (all CFCs, by professional discipline, for resource patients/parents, and for professionals) to search for potential associations between quality of care at the CFC 3 years after the PHARE-M intervention and the effectiveness of the QT and/or the engagement of parents/patients and/or contextual elements.

After the publication of the Registry report presenting the 2015 data, changes in indicators from 2011 to 2015 will be crossed with the results of the realistic part of the study, in an attempt to identify any association in relation with more favorable changes over time in patient outcomes. A “signature” set of factors associated with a maximum/minimum impact of the PHARE-M will be sought.

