### Limitations identified and initial lessons

As a result of the experimental study based on Registry data, a study population paired between two groups (intervention and control) was defined to eliminate certain confounding factors, especially factors linked to patient age distribution. Despite this pairing, significant differences remained in terms of patient age at diagnosis and primary endpoint (FEV1%) between the two groups before the intervention, in favor of the intervention group. These initial differences could have a favorable effect for the rate of decline in FEV1% in 4 years in the intervention group [22, 23]. The question is to investigate whether the slopes are parallel or not. The difference in FEV1% will be taken into account using two different intercepts in the model, one for the intervention group and one for the control group. The patients belonging to either the “PHARE-M” group or the “Control” group will be identified in the Patient Registry with respect to their group for further analysis of their health outcomes.

Moreover, on-site quality audits of the Registry data included in the calculation of the primary endpoints showed discrepancies, mainly due to the CFCs’ interpretation of the rule for selecting the values to transmit to the Registry [16]. The volume of the discrepancies identified in the data audited could be attributed to the change of the rule applied from the 2011 registry survey. This audit points out the need for a certification process to enable a larger use of this database in epidemiologic studies or for public health or pharmacovigilance purposes.

The survey conducted for the qualitative study of the multidisciplinary teams at the 14 centers should include around 130 respondents, including at most 14 patients/parents. This number of respondents might seem low for having enough statistical power in the statistical validation of the survey instruments, especially for the parts of the questionnaire developed within this research. The survey instruments could be improved within the framework of subsequent research studies aiming, for example, at comparing quality of care between centers trained in the PHARE-M and centers untrained in the program, or at making an assessment of the quality of care before/after another intervention. Therefore, this questionnaire represents an instrument that could have further uses in the network.

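### The plan promises PHARE-M's impact on care management, but care quality is scored once, in 2015, in trained centres only, so that impact cannot be estimated

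*Protocol article*

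**What the plan says.** Several places in the protocol article treat care management as something on which the programme's effect will be shown.

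- A mixed methodology: the rationale is "to show evidence of the performance of the PHARE-M program on patient outcomes and care management".
- Background: one research question is "What impact on care management can be observed in 2015". The next asks whether the time allowed was long enough for improvement to appear in both areas.
- Abstract, Methods: the realistic study offers "a characterization of the impact on care management and an identification of mechanisms through which the PHARE-M intervention improved the team’s effectiveness".
- Analyses of responses and validation of the questionnaire: the final step looks for a signature of factors that go with the largest or smallest impact.

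The measurement is narrower. Under Qualitative study, Design, the hypotheses are to be tested "using a questionnaire to be self-administered, in 2015, to all members of the MDT at the 14 CFCs", together with the patients or parents on the quality teams. On-site investigations gives one visit per centre: "The investigations conducted by the clinical research assistant at the 14 PHARE-M centers take place over the course of 2.5 consecutive days per CFC". For sample size, "the anticipated number of respondents is around 130 people in total for the 14 teams". Under Limitations identified and initial lessons, "comparing quality of care between centers trained in the PHARE-M and centers untrained in the program" is given as an example of what later research could do, as is a before/after assessment of care quality around another intervention.

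**The concern.** An impact or an improvement is a change, or a difference from what would have happened otherwise. A single score in trained centres is a level. The document itself gives reasons why that level could be high without PHARE-M. The 14 centres volunteered, and team motivation drove adherence. Contextual features that predate the programme may have strongly influenced its outputs. National work on multidisciplinary care, information systems and quality was under way from 2006.

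The reading matters because the Background says the assessment was expected in order to continue enrolment, and the Discussion says it is to feed recommendations for national roll-out. If a favourable 2015 score is reported under the heading of impact, readers may take a level for an effect. If trained centres are ranked by that score, a centre that was already strong will look like one in which the programme worked best.

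**Working it through.** The plan gives no effect size, power or target figure for care quality, so there is no figure to reproduce. The check is whether the planned data can identify an impact.

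**1. The instrument.** Table 4 lists 4 improvement-goal, 8 self-management, 14 multidisciplinary, 6 decision-support, 9 information-system and 6 community-network items: 4 + 8 + 14 + 6 + 9 + 6 = 47. The items describe the centre's current state. None asks what has changed since PHARE-M.

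**2. The timing.** Training ran from 2011 to 2013 (Background). The questionnaire was prepared from January to June 2014 and tested from July to September 2014 (Development of the instruments of the realistic study), then used in 2015. No trained centre can have a pre-intervention score on it.

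**3. The cells needed.** A controlled impact estimate is (trained 2015 − trained before) − (control 2015 − control before).

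| Care-quality score | Before PHARE-M | 2015 |
|---|---|---|
| Trained CFCs | not measured | measured (14 CFCs, about 130 respondents) |
| Control CFCs | not measured | not measured |

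One cell of four is filled. Neither the within-centre change nor the trained-versus-control difference can be formed. Under Quantitative study, Design, the before/after and control comparison covers patient health indicators only.

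**4. What one cell allows.** Scores are rescaled to 100, and a response of No or Unknown counts 0, so a mean lies between 0 and 100. If the trained mean in 2015 is S, the unmeasured earlier mean could be anything from 0 to 100, and the change lies between S − 100 and S. That interval contains zero for every possible S, even before any change in control centres is subtracted. More respondents make S more precise but do not narrow the interval.

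**5. Differences between trained centres.** For centre k, write the 2015 level as L = B + D, where B is the level before the programme and D the change since. For a factor X such as leadership or quality-team effectiveness, Cov(L, X) = Cov(B, X) + Cov(D, X). Only the sum is observable. Differential impact is the second term. The first is zero only if earlier care quality was unrelated to X. Qualitative study, Design points the other way: it says context that predates the programme may affect both adherence and outputs.

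**6. Other planned sources on change.** Focus groups at all 14 centres ask which organizational changes the team attributes to PHARE-M. Their results are to be set beside interviews with the first 7 centres, whose themes included effect on care management. These are accounts from trained teams, without a measured baseline or control. They support statements about perceived change.

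**The case against.** The strongest defence is that the qualitative arm was never meant to estimate a controlled effect. The Abstract's Background gives two aims: patient health indicators in trained versus untrained centres, and contextual reasons for variability among trained centres. For the second, a trained-only sample follows from the question. The questionnaire analysis is called descriptive and looks for potential associations, with no planned test of PHARE-M's effect on the score. The Discussion says that the centres volunteered and were not randomized, and leaves controlled comparisons of care quality to later work.

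Much of this stands. A reader might infer that the plan will compute an effect from the 2015 score. It does not: the analysis section describes levels and associations. A reader might also infer that the study can say nothing about change in care management. That too goes beyond the documents, because the focus groups and pilot interviews are planned sources on change as the teams perceive it.

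What the defence does not remove is the mismatch between those analyses and the stated claims. The variability aim is itself framed as a difference in impact among trained centres, and for care management only differences in level are available (step 5). The signature step crosses the questionnaire with 2011 to 2015 changes in patient indicators, which are true changes. The text does not confine impact to those indicators, so the care-quality level can be read as a second yardstick. The causal caveat in the Abstract's Conclusion concerns patient health indicators. The questionnaire limitation in the Discussion concerns the number of respondents. Neither says that care quality has no baseline and no comparator.

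**Conclusion.** The point holds for the care-management claim only. Of the four means needed, three are unmeasured, so a change in care quality attributable to PHARE-M cannot be estimated, and differences in 2015 score between trained centres cannot be separated from pre-existing differences. This rests on the instrument, timing and sites as the article states them, and on no other care-quality score being collected; the article mentions none.

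Two further inferences should be resisted. The FEV1% and BMI comparisons are not affected: they have a 2011 baseline and a control group. Nor do the documents support the idea that the Registry could supply a controlled test of care processes. Under Primary and secondary endpoints, treatment appears only as a possible patient category for analysing FEV1% and BMI, and nothing shows that the Registry holds suitable process indicators. The six dimensions scored are largely matters of team organization, which treatment data would not capture.

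**What to change.** Change the wording in four places: Abstract (Methods), Background (research questions), A mixed methodology (rationale), and Analyses of responses and validation of the questionnaire (the signature step). State the care-management aim as describing (a) the 2015 level of care quality in the trained centres, (b) its association with quality-team effectiveness and context, and (c) change as perceived by the teams in focus groups and pilot interviews. Drop impact and performance for care management. In the signature step, keep any language of change for the 2011 to 2015 patient indicators, and call the care-quality results associations with the 2015 level. The sentence under Qualitative study, Design that speaks of testing hypotheses needs the same qualification.

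Add to Limitations identified and initial lessons that care quality has no pre-intervention value and no control-centre value. Place this alongside the volunteer-centre caveat in Scope of the study and generalization.

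This needs no new data or analysis. The cost is a less favourable claim. Giving the questionnaire to control centres in 2015 would fill one more cell, but the baseline would still be missing and volunteer selection would remain, so it would not restore the impact claim.
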